### Sample size and power analysis

The sample size calculations were based on previously published data on increased lower extremity strength with MRE and ERT [47]. The rate of increase in the muscle strength during ERT is 5%–17% [34]. Positive correlations (*r* = 0.75) have been reported regarding the relevance of CS-30 scores on knee extension strength [47]. The average CS-30 score in patients with KOA is 9.2 repetitions [48]. Assuming that ERT can be expected to increase the CS-30 score by 13%, this sample size allows the detection of 1.2 times the primary outcome improvement (increased CS-30 score), in addition to an increase of 2.68 repetitions (1.90–3.47 repetitions, *p* < 0.001; I2 = 0.50%) due to the MREP alone [49]. The required sample size is 36 persons per group, calculated with an 80% one-sided test setting power, 5% alpha, and a 0.6 effect size (Cohen's d). The target size is set to 40 per group to account for a dropout rate of approximately 10%. Reports have shown that ERT has a low-to-moderate effect on lower extremity strength [34, 49, 50] and that ERT has improved knee pain and joint function in patients with KOA [29, 31]; therefore, we assume that ERT will have a slightly larger-than-moderate effect.

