### Statistical analysis

The MREP participants will be assigned to either the oestrogen or placebo group. Data will be aggregated for the assigned analysis participants at baseline, 3 months, and 12 months after the intervention. The target population will be the full analysis set, defined as all the randomised participants who have started their trial treatments.

The statistical analysis will be based on the intention-to-treat and per-protocol principles. The participants’ demographic background and baseline characteristics will be described as appropriate, with data presented as mean and standard deviation for continuous variables that appear to be approximately normally distributed, as medians and interquartile ranges for other continuous variables, and as counts and percentages for categorical variables. Linear regression analysis will be performed for a statistical comparison of the primary and secondary outcomes between the oestrogen and placebo groups. The relationship between the intervention and endpoints will be calculated as a regression coefficient with a 95% confidence interval. The covariate distribution is expected to be consistent across the groups due to randomisation. Therefore, only the presence or absence of intervention will be used as an explanatory variable for the linear regression analysis. However, the variable distribution will be biased by chance due to allocation; thus, the variable is added to the explanatory variables and an adjustment is made. We will adopt a complete case analysis as the primary analysis if the proportions of missing data are < 5%. Multiple imputations will be conducted if imputation of > 5% is required for the amount of missing data for an outcome, and the method will be reported.

The statistician, who is blinded to the allocation, will perform the analysis at the Department of Obstetrics and Gynaecology, Graduate School of Medicine, Dentistry, and Pharmaceutical Sciences, Okayama University. The validity of the analysis will be verified by the Centre for Innovative Clinical Medicine and Department of Epidemiology of the Okayama University as a third-party institution.

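### The sample size is powered for a one-sided 5% test, but the comparison is reported with a 95% confidence interval; if that interval decides, power is about 71%, not 80%

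*Protocol article*

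**What the plan says.** The protocol article, under Sample size and power analysis, sizes the trial as follows: "The required sample size is 36 persons per group, calculated with an 80% one-sided test setting power, 5% alpha, and a 0.6 effect size", the effect size being Cohen's d. It then allows for attrition: "The target size is set to 40 per group to account for a dropout rate of approximately 10" per cent.

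Under Statistical analysis, the two groups are compared by linear regression. By default, treatment is the only explanatory variable; another variable is added if chance leaves it unbalanced between the groups. The inferential output is described in one sentence: "The relationship between the intervention and endpoints will be calculated as a regression coefficient with a 95% confidence interval". That section gives no significance level, does not say whether the test is one-sided or two-sided, and mentions neither a one-sided bound nor a 90% interval.

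Two other places bear on how much this matters. Study design calls the trial exploratory, and the hypothesis under Aim is directional (an increase in the chair stand score).

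**The concern.** The test that fixes the sample size and the interval that reports the result do not correspond. A one-sided 5% test puts all of the 5% in the favourable direction. A 95% confidence interval, in its usual two-sided form, leaves only 2.5% there. The stated 80% belongs to the first rule and the planned output to the second.

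Two things are at stake. First, if readers and authors judge the result by whether the 95% interval excludes zero, the chance of missing a true effect of d = 0.6 is larger than the plan states. Second, there is a band of results that is significant one-sided at 5% although the reported interval includes zero. The article does not say which rule would govern there, so the conclusion could be chosen once the data are known.

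**Working it through.** **Inputs.** From Sample size and power analysis: d = 0.6 (so the SD is taken as 1), alpha 0.05 one-sided, power 80%, 36 evaluable per group, 40 enrolled per group, dropout about 10%. From Statistical analysis: regression on treatment alone, which is equivalent to a two-sample t-test, with a 95% interval. One reading is assumed: the 95% interval is two-sided with equal tails.

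**Formula.** With n per group, the degrees of freedom are 2n − 2 and the noncentrality is d × √(n/2). Power is the probability that a noncentral t variable exceeds the critical value: the 95th percentile of t for one-sided 5%, the 97.5th for two-sided 5%. The two-sided rule also has a lower tail, which is negligible here.

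**Step 1: reproduce the plan's figure (one-sided 5%).**
- n = 35: power 79.96%, just short of 80%.
- n = 36: noncentrality 0.6 × √18 = 2.546, critical value 1.667 on 70 df, power 80.9%.

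So 36 is the smallest n that reaches 80%, as stated. For dropout, 36 / 0.90 = 40, also as stated.

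**Step 2: same n, 95% interval excluding zero (two-sided 5%).**

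| Evaluable per group | Noncentrality | One-sided 5%: critical t, power | Two-sided 5%: critical t, power |
|---|---|---|---|
| 36 | 2.546 | 1.667, 80.9% | 1.994, 70.9% |
| 40 | 0.6 × √20 = 2.683 | 1.665, 84.5% | 1.991, 75.5% |

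The normal approximation gives 72.1% and 76.5% in the last column, so the conclusion does not depend on the method. The risk of missing a true d = 0.6 at 36 per group goes from 100 − 80.9 = about 19% to 100 − 70.9 = about 29%.

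**Step 3: what 80% would need two-sided.** 44 per group gives 79.5% and 45 gives 80.4%, so 45 evaluable per group, or 45 / 0.90 = 50 enrolled. This is given for scale only. The sample size calculation therefore reaches 36 only with the one-sided rule.

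**Step 4: the band where the two rules disagree.** At 36 per group the observed standardised difference must exceed 1.667 × √(2/36) = 0.39 to be significant one-sided, and 1.994 × √(2/36) = 0.47 for the 95% interval to exclude zero. If the true effect is d = 0.6, the result falls between the two with probability 80.9% − 70.9% = about 10% (84.5% − 75.5% = about 9% at 40 per group).

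**The case against.** The strongest reply is that no contradiction is written down. A 95% interval can be a reporting format only. A trial may declare a one-sided 5% test and still show a conventional 95% interval for estimation. The analysis section does not call the interval two-sided and does not say that success means excluding zero. This stands, and it makes the power figures conditional. A reader might infer that the trial simply lacks its stated power under its planned analysis; the article does not support that, because it never names the interval as the decision rule.

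A reader might also infer that the sample size was miscalculated. It was not: 36 and 40 both reproduce from the stated inputs.

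Nor is one-sidedness itself the fault. The sample size section discloses it, and the hypothesis is directional. Not repeating it in a condensed article would be no finding on its own, since a fuller protocol or analysis plan may state the rule. What remains is that the article fixes both a sizing test and a reporting interval, and the two do not match.

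The exploratory label lowers the consequence. It does not reconcile the two sections, because the trial still carries a formal power statement.

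Finally, it could be argued that adjusting for baseline would restore the power. The documents give no baseline-to-follow-up correlation, and the default model contains treatment only. As an illustration at 36 per group, if d = 0.6 applies to the change score, two-sided power with baseline adjustment would be about 75% at a correlation of 0.8 and about 83% at 0.5. Taking d = 0.6 on the follow-up score instead gives quite different figures. The documents do not support counting on that gain.

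**Conclusion.** The mismatch is real, in conditional form. The sizing is right for a one-sided 5% test; the only inferential output described for the comparison corresponds, in its usual sense, to a two-sided 5% test. If the 95% interval decides, power is about 71% at 36 evaluable per group and about 75% if all 40 are analysed, so even without dropout it stays below 80%. If the one-sided test decides, the stated 80% holds, but the reported interval does not show that decision.

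The figures assume d = 0.6, equal groups, the unadjusted comparison and a two-sided reading of the 95% interval. The estimate and its standard error are unaffected. This should be fixed, but in an exploratory trial where a sentence or two resolves it, it is not critical.

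**What to change.** Name one decision rule for the primary comparison in the Statistical analysis section before unblinding, and make the power statement match. Either option is coherent:

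- **Two-sided 5%, read from the 95% interval.** Restate the power in the sample size section as about 71% at 36 evaluable per group, or about 75% if all 40 are analysed, for the unadjusted comparison at d = 0.6.
- **One-sided 5%.** State in the analysis section that the primary test is one-sided at 5%, and report the matching 90% interval or one-sided 95% lower bound. The 36 per group and 80% then stand unchanged.

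If a gain from baseline adjustment is to be claimed, state the assumed correlation and the scale on which d = 0.6 is defined.

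The cost is wording in the protocol or analysis plan. No extra participants or visits are proposed. Under the first option the price is a less favourable power statement.

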### Statistical analysis

The MREP participants will be assigned to either the oestrogen or placebo group. Data will be aggregated for the assigned analysis participants at baseline, 3 months, and 12 months after the intervention. The target population will be the full analysis set, defined as all the randomised participants who have started their trial treatments.

The statistical analysis will be based on the intention-to-treat and per-protocol principles. The participants’ demographic background and baseline characteristics will be described as appropriate, with data presented as mean and standard deviation for continuous variables that appear to be approximately normally distributed, as medians and interquartile ranges for other continuous variables, and as counts and percentages for categorical variables. Linear regression analysis will be performed for a statistical comparison of the primary and secondary outcomes between the oestrogen and placebo groups. The relationship between the intervention and endpoints will be calculated as a regression coefficient with a 95% confidence interval. The covariate distribution is expected to be consistent across the groups due to randomisation. Therefore, only the presence or absence of intervention will be used as an explanatory variable for the linear regression analysis. However, the variable distribution will be biased by chance due to allocation; thus, the variable is added to the explanatory variables and an adjustment is made. We will adopt a complete case analysis as the primary analysis if the proportions of missing data are < 5%. Multiple imputations will be conducted if imputation of > 5% is required for the amount of missing data for an outcome, and the method will be reported.

The statistician, who is blinded to the allocation, will perform the analysis at the Department of Obstetrics and Gynaecology, Graduate School of Medicine, Dentistry, and Pharmaceutical Sciences, Okayama University. The validity of the analysis will be verified by the Centre for Innovative Clinical Medicine and Department of Epidemiology of the Okayama University as a third-party institution.

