### Randomisation, allocation, and blinding procedure

Each participant will be enrolled in this trial by investigators after the medical assessment and matching the inclusion and exclusion criteria. The investigator will provide each participant with an identification code according to the case enrolment order and fill out a registration sheet, which includes the date of obtaining consent, any other information necessary to match the participant with the corresponding identification code, and the factors used for stratified randomisation.

The participants will be randomly categorised into two groups by an allocator who will not have contact with them throughout the trial: (1) MREP with transdermal oestrogen gel and (2) MREP with placebo gel. The participants will be stratified according to age (older: 75–89 years, younger: 65–74 years), physical activity (the intermediate steps taken in a week measured by a pedometer, higher ≥ 5000 steps per day, lower < 5000 steps per day), and knee extension strength (higher ≥ 18 kgf, lower < 18 kgf). The randomisation schedule will be computer-generated using the randMS® mobile application [46] (sold by [name], created using Filemaker® and Filemaker Pro Advanced®, ©2019 kazenoan) with a mixture of two or more block sizes. The allocator will send an email with the trial group allocation result and participant identification codes to an unblinded pharmacist who will fill the placebo gel into the supplement bottles and label them according to the group allocation. In the unlikely event of an adverse symptom requiring further medical investigation, the gel allocation details can be accessed by the investigator, and the patient will be excluded from the trial.

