### Outcome assessment

Outcome assessment will include baseline measurements of participants' anthropometric data and outcomes. At baseline, a physiotherapist will measure the height, weight, and upper arm, thigh, calf, abdominal, and gluteal circumferences and calculate the body mass index (BMI). The resting blood pressure and heart rate will be measured simultaneously. Outcome examinations will be performed at baseline before allocation, and 3 and 12 months after intervention initiation (Fig. 1). Outcomes will be measured by physical therapists with at least 5 years of clinical experience.

The primary outcome will be the 3-month and 12-month changes from the baseline physical performance according to the CS-30 score. The CS-30 devised by Jones is highly reproducible and has been shown to correlate with the quadriceps muscle strength and the ability to balance, walk, and perform ADL [61]. Since KOA-related knee pain reduces the ability to perform vertical movements, CS-30 is also reliable for functional assessment of inactivity due to KOA [62]. CS-30 uses an armless folding chair with a seat height of 40 cm. The participants will be seated in the middle of the chair with their back straight, feet shoulder-width apart, and arms crossed at the chest, and will be encouraged to complete as many full stands as possible within 30 s [61]. They will be instructed to sit fully between each stand. The measurer will silently count the correct stand completions after letting the participant practice once or twice.

The secondary outcomes include:Change in the knee pain score assessed using the VAS and 12-item Short form survey (SF-12).

VAS will be used to assess knee joint pain before and after the intervention. The pain intensity will be indicated by a 10 cm black line (the left end for ‘no pain’ and right end for ‘the greatest pain imaginable’) on the questionnaire, and the participant will be asked to draw a line to indicate the level of her current pain. Health-related quality of life as pain in daily life will be assessed using the SF-12, which was validated as a shorter alternative to the SF-36 [63].2)Change in physical function according to the gait speed and timed up and go test (TUGT)

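### The treatment-only primary regression leaves out baseline CS-30 and the three stratification factors and adds covariates on observed imbalance; fixing the covariates in advance would be a free gain in precision

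*Protocol article*

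**What the plan says.** The Statistical analysis section of the protocol article plans a linear regression for primary and secondary outcomes. Because randomisation is expected to balance covariates, "only the presence or absence of intervention will be used as an explanatory variable for the linear regression analysis". The next sentence qualifies this: "the variable distribution will be biased by chance due to allocation; thus, the variable is added to the explanatory variables and an adjustment is made". It names no variable, no criterion for imbalance and no time at which the decision is taken.

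The section on randomisation, allocation and blinding states "The participants will be stratified according to age" and goes on to list physical activity (5000 steps per day) and knee extension strength (18 kgf) as further factors. None of the three is in the model.

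Under Outcome assessment, "The primary outcome will be the 3-month and 12-month changes from the baseline physical performance according to the CS-30 score". Outcomes are measured at baseline before allocation. Baseline CS-30 therefore enters by subtraction but not as a covariate.

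The sample size was "calculated with an 80% one-sided test setting power, 5% alpha, and a 0.6 effect size" (Cohen's d), and "The required sample size is 36 persons per group". The same section cites a correlation of 0.75 between CS-30 score and knee extension strength.

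**The concern.** Expected balance is not a reason to leave prognostic covariates out. Three consequences follow.

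- **Efficiency.** A change score removes only part of the variation due to baseline. Adding baseline CS-30 as a covariate removes more whenever the baseline/follow-up correlation is below 1.
- **Standard error.** Stratified allocation reduces the true variance of the treatment estimate when the strata predict the outcome. A treatment-only model does not credit that reduction, so its standard error is too large.
- **Prespecification.** If a variable enters because it turned out imbalanced, the primary model is settled after looking at the data. With no list and no threshold, either an adjusted or an unadjusted estimate could be presented as the planned one.

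At stake are some precision in an 80-participant trial and a clear definition of the primary estimate.

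**Working it through.** **Inputs from the article:** one-sided alpha 5%, power 80%, d = 0.6, 36 per group, 40 after dropout; primary outcome is change in CS-30; model contains treatment only; correlation of CS-30 with knee extension strength 0.75.

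**Assumptions:** the baseline/follow-up correlation of CS-30 (ρ) is not given, so a range is used. d = 0.6 is taken on the SD of change, which the article does not specify. Baseline and follow-up variances are equal.

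**1. The article's own figure.** With n per group, the noncentrality is d·√(n/2) = 0.6·√18 = 2.546 on 70 df. One-sided power is 80.9%, and 36 is the smallest n that reaches 80% with the t-test. For dropout, 36/0.9 = 40. The stated size is right for an unadjusted one-sided comparison. At the two-sided 5% level that matches a 95% interval, power at 36 per group is 70.9%.

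**2. Gain from adjusting for baseline CS-30.** The variance of change is 2σ²(1−ρ). The residual variance after adjustment is σ²(1−ρ²). Their ratio is (1+ρ)/2, so the effective d is 0.6/√((1+ρ)/2). For example, at ρ = 0.5 it is 0.6/√0.75 = 0.693. One degree of freedom is spent.

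| ρ (assumed) | Variance ratio | Interval width ratio | One-sided power, n = 36 | Two-sided power, n = 36 | n per group for 80% one-sided |
|---|---|---|---|---|---|
| unadjusted | 1 | 1 | 80.9% | 70.9% | 36 |
| 0.5 | 0.75 | 0.866 | 89.7% | 82.6% | 27 |
| 0.7 | 0.85 | 0.922 | 86.2% | 77.7% | 30 |
| 0.8 | 0.90 | 0.949 | 84.4% | 75.4% | 32 |
| 0.9 | 0.95 | 0.975 | 82.7% | 73.1% | 34 |

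The one-sided gain runs from 82.7 − 80.9 = 1.8 points to 89.7 − 80.9 = 8.8 points.

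**3. How much the strata can explain.** The 0.75 refers to CS-30 levels. If strength relates to follow-up only through baseline CS-30, it explains 0.75²·(1−ρ)/2 of the variance of change: 0.5625 × 0.25 = 14% at ρ = 0.5 and 0.5625 × 0.10 = 6% at ρ = 0.8. Splitting strength at about its median multiplies this by about 0.64, giving roughly 9% and 4%.

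**4. Simulation under stratified allocation.** Settings: 36 per arm, eight strata, blocks of 2 and 4, 6000 runs per scenario, correlation 0.75 between strength and baseline CS-30, and assumed correlations of magnitude 0.3 for age and activity. The three models are treatment only; treatment with baseline CS-30 and the three strata; and a rule that adds any of these covariates whose baseline comparison has p < 0.05.

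| ρ | Mean SE / true SD, unadjusted | Two-sided type I error: unadjusted / prespecified / rule | One-sided power: unadjusted / prespecified / rule |
|---|---|---|---|
| 0.5 | 1.050-1.066 | 4.0 / 4.8 / 3.9% | 83.0 / 90.0 / 83.3% |
| 0.7 | 1.024-1.039 | 4.1 / 5.2 / 4.1% | 82.0 / 86.2 / 82.2% |
| 0.8 | 1.011-1.020 | 4.1 / 4.8 / 4.1% | 81.8 / 84.4 / 81.9% |

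The Monte Carlo standard error is about √(0.04 × 0.96/6000) = 0.25 points for the error rates and about 0.5 points for power. Coverage of the unadjusted 95% interval is about 100 − 4 = 96%. Unadjusted power is slightly above 80.9% because stratification has already reduced the true variance. The power gain here is therefore 7.0, 4.2 and 2.6 points. The imbalance rule recovers almost none of it.

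**The case against.** The strongest reply is that nothing here is invalid. An unadjusted comparison of change scores is unbiased under randomisation, the stated sample size matches the stated analysis, and the trial calls itself exploratory. The power forgone is measured against a better model, not against the plan's own target. All of this stands, and it limits the weight of the point.

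Three stronger readings are tempting, and the documents do not support them.

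- A reader might infer that intervals which miss their nominal coverage are too narrow. The error goes the other way: mild over-coverage and a conservative test.
- A reader might take the 0.75 to mean that the strata explain a large share, say 30%, of outcome variance. It concerns levels, whereas the outcome is change. Under the assumption in step 3, strength accounts for at most about 6-14%. If strength correlated equally with baseline and follow-up, it would explain none of the change.
- A reader might infer that the imbalance rule inflates type I error. The one explicit rule tried did not (3.9-4.1%).

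The article also provides a statistician blinded to allocation and third-party verification. These limit discretion but do not define the model. The sentence on adding variables is garbled: taken literally, it asserts that imbalance will occur, which contradicts the sentence before it. The conditional reading is the natural one. On either reading it is unclear which model is primary.

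Finally, covariate details are often left to an analysis plan that is not shown here. That would answer a complaint about missing detail, but the article affirmatively states a treatment-only model and an imbalance-triggered exception.

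**Conclusion.** The point holds as a free improvement, not as an error that invalidates the trial. The planned analysis is unbiased and meets its stated 80% one-sided power. Compared with adjustment for baseline CS-30, it gives up about 2 to 9 points of power, depending on an unknown baseline/follow-up correlation between 0.9 and 0.5. Leaving out the strata makes the standard error about 1-7% too large, with coverage near 96%. The model remains dependent on observed imbalance; the harm is an undefined primary estimate, not a demonstrated excess of false positives.

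The power figures rest on d = 0.6 being on the SD of change and on equal variances at baseline and follow-up. The standard-error and coverage figures rest also on the simulated correlations and on strata split at the median.

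**What to change.** Replace the two sentences, on the treatment-only model and on adding variables, with:

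> For each primary time point (3 and 12 months), change in CS-30 will be analysed by a linear model on treatment, baseline CS-30 (continuous) and the three binary stratification factors. These covariates are fixed in advance and none is added because of observed imbalance. The unadjusted comparison is a sensitivity analysis. Secondary outcomes use the same model with their own baseline value.

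The wording covers both time points because the article makes both changes primary. It settles binary against continuous strata because leaving that open would restore the analyst's choice.

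The cost is wording and about 4 of roughly 70 degrees of freedom. Baseline CS-30 and the three factors are all obtained before allocation, so no data collection changes. The sample size can stay as it is.
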